### Benefits

This is a research study, and the potential benefit of this vaccine as a cancer treatment is entirely unknown. However, the patient will be involved in the testing of a new therapeutic approach. The patient will receive intensive exposure to medical staff and care. Patients enrolled in this study will be offered the opportunity to enroll in subsequent studies to further evaluate toxicity and efficacy of this vaccination.

### Risks and complications

The most likely risk from participation in this study is pain and swelling at the site of inoculation. There are also risks associated with blood drawing and leukapheresis that all study subjects may anticipate. The risks associated with leukapheresis and immunization may be considered separately.

#### Risks associated with Leukapheresis

Leukapheresis is a means of drawing blood meant to save the subject multiple blood draws and loss of RBCs. Leukapheresis is a procedure very much like blood donation for the subject. A needle is placed in the arm, and blood is collected as in the blood bank. Unlike blood donation, however, the patient’s own red blood cells, platelets and plasma are returned to the patient, which helps to prevent anemia. Only the patient’s white blood cells are kept for clinical study. Less than 1% of an individual’s white blood cells are normally in circulation, and ready pools are available in the spleen and lymph nodes to replenish donated white blood cells, so that the cells removed at leukapheresis are replenished by the patient almost immediately.

The risks involve the use of an invasive needle, which may lead to bruising of the arms where the needle is placed, and which may lead to the introduction of bacteria and infection. There is a minor risk of bleeding from anticoagulants given during the procedure; this anticoagulant (citrate) is broken down by the body within one minute, any bleeding will be stopped by terminating the leukapheresis. The citrate may cause mild, transient hypocalcemia, which may be associated with symptoms of tingling or muscle cramping. Rarely, patients may faint (suffer hypotension due to a vasovagal reaction) during leukapheresis; for this reason patients lie down during the procedure and are accompanied at all times by medical staff. Patients who are taking ACE inhibitors will have their dose held until after the leukapheresis procedure is completed. Patients sometimes feel chilled during leukapheresis; if they do, they will be given blankets to keep warm.

Needles used for leukapheresis may be placed in the veins in the arm. In patients for which insufficient venous access is available in the arms, needles may instead be placed in larger veins, typically the femoral vein located at the top of the leg. These needles entail the same kinds of risks as needles placed in the arm (bleeding, infection), but has a risk of producing large hematomas in the leg, and may be less comfortable than needles placed in the arm.

#### Risks associated with immunization

There is a risk of local vaccine injection site reactions. It is likely that temporary pain, redness, and swelling will develop at the injection sites. If needed, ice packs or oral acetaminophen will be used to treat this.

There is slight risk of infection from the injection of DCs. To minimize this risk, the vaccine will be manufactured in a laboratory governed by Good Laboratory Practice principles and in biosafety cabinets. There are no known alternatives to the protocol described to generate dendritic cells loaded with multiple prostate tumor cell antigens. Although the experiments are novel in design, the risks of an infusion of autologous cells pulsed with apoptotic LNCaP cells should be minimal. This includes an allergic reaction and the induction of autoimmunity. An allergic reaction is unlikely given that the patient’s own cells are being given back. Care is taken in the protocol to prepare the patients’ DCs in autologous plasma to reduce the possibility of an allergic reaction. In the event of an allergic reaction, the patient will be treated with appropriate medications (epinephrine, benadryl) if indicated and watched closely during the hospital stay.

DCs pulsed with individual peptides have been given to over 100 normal volunteers and cancer patients at the Rockefeller University GCRC and at outside institutions, with no evidence of adverse immune responses other than minor pain and redness at the sites of injection.

An immune reaction to LNCaP cells has been attempted in several tumor immunotherapy protocols done by other groups (although not apoptotic LNCaP cells pulsed onto DCs), as a desired means of inducing tumor immunity. The antigens present in LNCaP cells that are substantially different from the patient’s own set of proteins may elicit an immune response. This may lead to a reaction against LNCaP cells, and a reaction to other cells expressing such proteins. It is believed in this protocol that the other cells present in the patient’s body that are expressing such LNCaP antigens are the patient’s prostate cancer cells. Whether a reaction against other cells in the patient’s body may occur is unknown, and constitutes the basis of the risk for developing autoimmunity. The investigators believe this risk to be low. T cells capable of reacting with normal self antigens are believed to be deleted at birth or tolerized (inert) during the course of the patient’s lifetime. Given these considerations and the experience of other physicians with dendritic cell vaccines, the risk of autoimmunity, while unmeasurable, is considered to be small.

While we do not anticipate significant toxicity, the experiments will proceed with the following cautions. To watch for evidence of adverse reactions, including allergic or autoimmune reactions, patients will be closely monitored during the first hour after each vaccination. The local injection site and draining lymph nodes will be monitored for inflammation and swelling. A battery of tests for adverse reactions will be carried out at frequent intervals during the trial.

#### Balance of risk:benefit.

The balance of the risks versus benefits involved in participation are judged by the investigators to be clearly in favor of the benefits derived from participation. The risks are judged overall to be moderate, but are not anticipated to include serious adverse reactions. This is a research study, and the potential benefit of this vaccine as a cancer treatment is entirely unknown. The benefits include the intensive health care monitoring patients will receive, as well as the potential that if this protocol proves safe, patients will be offered the opportunity to enroll in subsequent studies to further evaluate toxicity and efficacy of this vaccination.

### Withdrawal from study

Patients are entitled to withdraw from this study at any time. The investigators may withdraw patients from this study who develop serious adverse reactions to the vaccine. All patients who withdraw from the study will be asked to continue to be followed as specified in the protocol.

### Stopping rules

#### Criteria for Subject Study Discontinuation

- Development of an exclusionary condition as outlined in section (6)i.e.2, prior to or during vaccination, with the following exceptions:
  - a course of palliative radiation treatment during the study
- platelet counts that drop > 50% from baseline.
  - hemoglobin that drops sufficiently to require transfusion.
  - if the patient develops an infection requiring treatment as an inpatient.
- Failure by the subject to attend three consecutive clinical study visits.
- Request by the subject to withdraw.
- Clinical reasons judged by the study physician to be life threatening, even if not addressed in the toxicity management of the protocol.
- Completion of week 17 or in some patients, week 29 in Arm 1.
- Completion of week 25 or in some patients week 37 in Arm 2.
- Any dose limiting toxicity. A dose limiting toxicity is defined as:
  1. any grade 2 or greater allergic toxicity or asymptomatic bronchospasm or generalized urticiaria
  2. any grade 3 or greater toxicity (hematologic or non-hematologic)
  3. any grade 2 or greater autoimmune reactions

If a subject discontinues prior to completion of the study, the reason for and date of the discontinuation will be recorded. The date of the last dose of study vaccine will also be recorded. Subjects who discontinue prior to study completion may be replaced at the discretion of the Investigator.

#### Vaccine Toxicity

The Common toxicity Criteria (CTC) version 3.0 (http://ctep.info.nih.gov) grading system will be used for grading the severity of adverse events. For adverse events not covered by the CTC grading system, the following definitions will be used:

Table 3. Grading and Attribution of Local Reactions to Vaccine

| Grade | Symptoms | Signs |
| --- | --- | --- |
| 0 = None | No pain or tenderness (VAS 0) | N/A |
| 1 = Mild | Minimal pain or tenderness, no limitation of arm use (VAS 1-3), mild warmth | Erythema or induration less than 15 x 15 cm (225 cm2) |
| 2 = Moderate | Notable pain or tenderness, some limitation of use of arm (VAS 4-7), moderate warmth | Erythema, induration or edema > 15 x 15 cm (225 cm2) |
| 3 = Severe | Extreme pain or tenderness, complete limitation of use of arm (VAS 8-10), hot | Ulceration, superinfection or phlebitis |
| 4 = Potentially life threatening | N/A | Necrosis of the skin |

The Investigator will also asses the relationship of any adverse event to the use of study drug, based on available information, using the following NCI-based attribution guidelines:

| Attribution | Description |
| --- | --- |
| Unrelated | The adverse event is CLEARLY NOT RELATED to the investigational agent. |
| Unlikely | The adverse event is DOUBTFULLY RELATED to the investigational agent. |
| Possible | The adverse event MAY BE RELATED to the investigational agent. |
| Probable | The adverse event is LIKELY RELATED to the investigational agent. |
| Definite | The adverse event is CLEARLY RELATED to the investigational agent. |

Note: it is anticipated that study patients will experience transient tenderness, redness or swelling at the local site of vaccine injection or DTH testing. Subjects should be told prior to administration that these anticipated reactions might occur. The subjects will be closely monitored following each immunization.

Local reactions (Grade 1-2)

Local reactions of mild (Grade 1) or moderate (Grade 2) severity will generally resolve without treatment. If needed, they may be managed with local application of ice packs or oral acetaminophen.

Local reactions (Grade 3-4)

Severe (Grade 3) or potentially life threatening (Grade 4) local reactions, the Rockefeller University GCRC Clinical Research Officer ([name]) must be notified within 48 hours. For grade 4 local reactions, definitive medical and/or surgical intervention should be undertaken as appropriate. Following Grade 3 or Grade 4 local reaction, further vaccines should not be given to other patients prior to consultation with the Rockefeller University GCRC Clinical Research Officer ([name]), and by the PI in conjunction with the Rockefeller Universities Institutional Review Board (IRB).

Systemic reactions

Systemic reactions will be graded according to the CTC version 3.0 (http://ctep.info.nih.gov).

All nonlocal Grade 3 or 4 reactions (for example, elevated temperature following immunization) thought definitely, possibly or probably related to vaccination, will be reported within 48 hours to the Rockefeller University GCRC Clinical Research Officer ([name]). Further vaccines should not be given to other patients prior to consultation with the Rockefeller University GCRC Clinical Research Officer ([name]), and by the PI in conjunction with the Rockefeller Universities Institutional Review Board (IRB).

The study will be stopped if 1 of 3, 2 of 6, 3 of 9, or 4 of 12 subjects experience dose limiting toxicity as defined under 6.i.m. Stopping rules, 1) Criteria for Subject Study Discontinuation. This applies to subjects in both Arm 1 and 2 while he is receiving the investigational product.

If a patient is injected with a DC-vaccine prior to knowing that a contaminant was present (e.g. prior to a 14-day culture becoming positive), the patient will be immediately contacted and undergo a complete history and physical examination. Blood cultures and appropriate laboratory tests will be drawn.

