Arm 2 (placebo followed by vaccine):

Weeks 1, 3, 5 and 7 Either saline or vaccine vehicle alone (5% DMSO in sterile saline) is given SQ in single injections of 500 l. At week 9, 11, 13, and 15 autologous DCs co-cultured with apoptotic irradiated LNCaP cells are given SQ in single injections of 500 l. At each of these latter times, autologous DCs co-cultured with apoptotic irradiated LNCaP-M1 cells, as well as either saline or vaccine vehicle alone (5% DMSOin normal saline ) are given SQ in single injections of 500 l. On weeks 9 and 11, autologous DCs exposed to KLH are also given SQ. The SQ injections may be given +/- 3 days from the scheduled visit, with the exception that the first injection, which will be given on day 8 (preferably) or day 9 after the patient completes leukapheresis.

Administration of Vaccine

The DC/LNCaP vaccine is given approximately 6-8 cm from the axilla in the inner aspect of the upper arm. The DC/LNCaP-M1 vaccine is given approximately 6-8 cm from the axilla in the inner aspect of the patients’ contralateral upper arm. The administration site is prepared with betadine and alcohol swabs. Injection is given with a 25-gauge needle by superficial SQ injection (not in the fatty part). DCs exposed to KLH and either saline or vaccine vehicle alone may be given in the anteromedial thigh approximately 12-24 cm distal to the inguinal ligament.

Immunologic Studies

DTH: DTH will be performed at the Rockefeller University GCRC, concurrent with each vaccination and at 2 weeks, 10 weeks and in some patients, at 22 weeks post last vaccination. DTH reactions will be read at the Rockefeller University GCRC between 40-48 hours after implantation. Results will be recorded on the CRF.

Lymphoproliferative responses, ELISPOT and CTL: Assays will be performed at the Rockefeller University.

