###### Delayed type hypersensitivity (DTH) responses

At screening, patients will be assessed for DTH response to positive control antigens (a standard “anergy panel” to include candida, trichopyton and tetanus). Patients with no positive response to the anergy panel are not eligible for trial entry. Responses to one of the anergy panel antigens will be subsequently used as a positive control non-modulated antigen. Each antigen will be placed subcutaneously using a tuberculin syringe to inject a volume of 100 l.

DTH responses during the study will be to the control non-modulated antigen and to various vaccine components, specifically the control immunizing antigen KLH, and to aliquots of killed LNCaP cells and LNCaP-M1 cells, to DC/LNCaP cells and DC/LNCaP-M1 cells, and as negative controls, to DCs which have not been peptide pulsed and to saline. DTH response will be assessed by measuring the region of induration surrounding the injection site of each antigen. Each antigen will be placed according to a stereotyped grid, and induration will be read between 40 and 48 hours after injection.

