#### Interim and Final Analysis

Preliminary safety analysis will be performed after each immunization is given. A final analysis will occur after all visits are completed. Final analysis will include an assessment of the relationship between the total number of dendritic cells administered and PSA levels as well as total number of dendritic cells administered and immunologic responses.

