#### Monitoring Adverse Events

Subjects having adverse events will be monitored with relevant clinical assessments and laboratory tests as determined by the Investigator. All adverse events must be followed to satisfactory resolution or stabilization of the event(s).

Any actions taken and follow-up results must be recorded on the appropriate Case Report Form, as well as in the subject’s source documentation. Follow-up laboratory results should be filed with the subject’s source documentation.

For all adverse events that require the subject to be discontinued from the study, relevant clinical assessments and laboratory tests will be repeated on at least a weekly basis, until final resolution or stabilization of the event(s).

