#### Serious Adverse Events

All serious adverse events (defined below), whether or not deemed drug-related or expected, must be reported by the Principal Investigator or designee to the IRB within 24 hours (one working day) by telephone, and to the GCRC Clinical Research Officer. Written reports must follow as soon as possible, which include full descriptions of the event and any sequelae. The PI will report any unexpected and serious adverse event within 7 calendar days by phone or fax to the FDA, and follow within 15 calendar days by written form to the FDA. Any actions taken by the FDA or IRB will be reported by the PI to the NCI.

These stipulations includes serious adverse events that occur any time after the inclusion of the subject in the study (defined as the time when the informed consent is signed), up to 30 days after the subject completes or is discontinued from the study. The subject is considered completed after the completion of the last visit, either as documented in the Study Flow Chart of the protocol. Discontinuation is the date a subject and/or Investigator determines that the subject can no longer comply with the requirements for any further study visits or evaluations (eg the subject is prematurely discontinued from the study; see Stopping rules).

A serious adverse event in this study is defined as any event that:

Is fatal,

Is life-threatening (defined as the patient being at immediate risk of death from the AE as it occurred),

Is significantly or permanently disabling,

Requires in-patient hospitalization, or prolongs hospitalization.

Important medical events that may not fit these criteria may also be considered a serious adverse drug experience when, based upon appropriate medical judgment, they may jeopardize the patient and may require medical or surgical intervention to prevent one of the outcomes listed in this definition.

In addition to reporting serious and unexpected adverse events to the FDA, the PI will also submit in a written report any finding from tests in laboratory animals that suggests a significant risk for human subjects including reports of mutagenicity, teratogenecity, or carcinogenicity within 15 calendar days of the PI’s initial receipt of the information.

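### The DLT stopping count has no stated end after dose 4; read literally, a delayed, related, non-serious Grade 2 allergic or autoimmune DLT has no study-level trigger

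*Combined protocol and SAP*

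**What the plan says.** Section (6)i.m, Vaccine Toxicity, sets the study-level DLT boundaries (1 of 3, 2 of 6, 3 of 9, 4 of 12) and then gives their scope: "This applies to subjects in both Arm 1 and 2 while he is receiving the investigational product". The DLT definition, under Criteria for Subject Study Discontinuation, covers Grade 2 or higher allergic toxicity, Grade 3 or higher toxicity of any kind, and "any grade 2 or greater autoimmune reactions". The definition has no time limit.

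DC vaccinations fall at weeks 1, 3, 5 and 7 in Arm 1 and weeks 9, 11, 13 and 15 in Arm 2 (Dosing Plan). The Duration section follows everyone to week 17 or 25. It treats a patient as having completed the study at 13 or 21 weeks, and follows only selected patients to week 29 or 37. DTH tests are placed "concurrent with each vaccination and at 2 weeks, 10 weeks and in some patients, at 22 weeks post last vaccination" (On-study evaluations). The DTH section lists the materials used during the study, among them KLH and responses "to aliquots of killed LNCaP cells and LNCaP-M1 cells, to DC/LNCaP cells and DC/LNCaP-M1 cells".

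SAE reporting, by contrast, has a stated end: "up to 30 days after the subject completes or is discontinued from the study" (Serious Adverse Events).

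**The concern.** A stopping rule should give the same answer whoever applies it. Here the boundaries are exact but the counting period is not. On the literal reading, a reaction two days after dose 1 counts and the same reaction two days after dose 4 does not. On the other reading, only Arm 2's placebo weeks are left out, and the text still does not say when counting stops.

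The product has not been given to humans before, autoimmunity is a named risk, and the plan gives autoimmune events their own lower Grade 2 threshold. If that threshold applies only during the six weeks of dosing, delayed events of that kind lose the trigger that was set for them. Stopping the individual subject after dose 4 withholds no further vaccination from him and does nothing by itself for patients still being dosed.

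**Working it through.** **The plan's own figures.** No error rate is stated for the DLT rule. The nearest stated figures are the one-sided Fisher p-values behind the separate SAE rule (Biostatistical analysis, 12 per arm), and they reproduce:

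- 3 v 0: C(12,3)/C(24,3) = 220/2024 = 0.109
- 4 v 1: (495 × 12 + 792)/42504 = 0.158
- 5 v 1: (792 × 12 + 924)/134596 = 0.077

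That rule counts SAEs only, so it cannot register a non-serious Grade 2 DLT.

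**Calendar** (Dosing Plan, Duration).

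| Interval | Arm 1 | Arm 2 |
|---|---|---|
| First to fourth DC dose | 7 − 1 = 6 weeks | 15 − 9 = 6 weeks |
| Dose 4 to completion | 13 − 7 = 6 weeks | 21 − 15 = 6 weeks |
| Dose 4 to end of planned follow-up | 17 − 7 = 10 weeks | 25 − 15 = 10 weeks |
| First dose to end of planned follow-up | 17 − 1 = 16 weeks | 25 − 9 = 16 weeks |

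Outside the literal window lie 10/16 = 62.5% of planned weeks, or 6/12 = 50% of the weeks up to completion. These are shares of calendar time, not of risk.

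**DTH sessions after dose 4.** These fall at weeks 7 + 2 = 9 and 7 + 10 = 17 (Arm 1), and 15 + 2 = 17 and 15 + 10 = 25 (Arm 2). Completion at week 13 or 21 reaches only the first, so it assures 24 × 1 = 24 sessions. Both sessions, 24 × 2 = 48, need every patient to stay to week 17 or 25.

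**Which rule reaches a related, non-serious Grade 2 DLT after dose 4?**

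| Provision | Condition | Study-level trigger for this event? |
|---|---|---|
| DLT count | DLT while receiving product | Not on the literal reading |
| 48-hour notice and hold on other patients | Grade 3 or higher | No |
| SAE stopping rule | SAE | No |
| Subject discontinuation | Any DLT | No, that subject only |
| Safety analysis after each immunization; monthly team review | Judgment, no numeric threshold | Discretionary |

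**Timing of the one cited late signal.** The section on safety and efficacy of DC and tumor cell vaccines reports a transient 1:40 ANA at 60 days in an earlier DC study, without clinical autoimmunity. 60/7 = 8.6 weeks. This exceeds the 6-week dosing span, so the same delay from any dose, even the first (week 1 + 8.6 = 9.6 in Arm 1), falls after the literal window closes. Measured from dose 4 it lands at week 15.6 or 23.6, within planned follow-up but past completion.

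**Effect on the rule.** At the 1-of-3 boundary one event decides: one reading stops the study and the other continues it. As a sensitivity check, assume a total DLT risk per subject and a share arising after dose 4, neither of which is in the documents. Exact binomial stopping probabilities over the first 12 subjects are:

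| Assumed total risk | All counted | 25% late, uncounted | 50% late, uncounted |
|---|---|---|---|
| 20% | 0.58 | 0.44 | 0.30 |
| 30% | 0.79 | 0.64 | 0.44 |

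The table covers DLTs of every grade. It therefore overstates the lost protection, because late Grade 3 or higher reactions still trigger the hold.

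**Why a longer window needs a relatedness condition.** Take the plan's 5% placebo SAE incidence as a stand-in for background DLTs (an assumption), over T = 8 or 9 weeks. The risk over W weeks is 1 − 0.95^(W/T).

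- W = 6: 3.8% or 3.4%, giving a stopping probability of 0.113 or 0.101.
- W = 16, unfiltered: 9.8% or 8.7%, giving 0.291 or 0.261.

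With correct attribution after the last dose, the background contribution stays at 10–11%.

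**The case against.** The best defence is that the sentence exists because Arm 2 has a placebo phase, and its ordinary purpose is to keep placebo weeks out of the count. The DLT definition it relies on has no time limit, and the literal reading gives an odd result at dose 4. In addition, if vaccine cells are injected as DTH tests after dose 4, the subject is arguably still receiving product, which would carry the window to week 17 or 25. Both points are fair, and the intended meaning may well be the sensible one. But neither supplies an end point, and the second depends on what is injected at each late visit.

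A reader might infer that vaccine cells are certainly given again after dose 4. The documents do not settle this. The DTH section lists materials for the study as a whole, and the visit-level schedule (Table 2) is not shown in the text available.

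The safeguards are also substantial. Beyond SAE and Grade 3 coverage, the plan allows that "Important medical events that may not fit these criteria may also be considered a serious adverse drug experience". A subject discontinued for an adverse event has follow-up in which "relevant clinical assessments and laboratory tests will be repeated on at least a weekly basis". ANA, dsDNA and RF are measured serially, the AE log is reviewed monthly, and "Preliminary safety analysis will be performed after each immunization is given", which recurs as later patients are dosed. All of this stands and narrows the gap to one class of event. None of it is a study-level trigger for that class.

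**Conclusion.** The point holds in a narrow form. The DLT count has no stated end after dose 4. On the literal reading, a delayed, related, non-serious Grade 2 allergic or autoimmune DLT has no study-level trigger, while Grade 3 or higher reactions and SAEs remain covered. The period at issue is 10 planned weeks per patient, of which completion assures 6, with one assured post-dose DTH session each.

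Three stronger inferences are not supported:

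- That late clinical toxicity is likely. The cited signals are a transient low-titer ANA without clinical autoimmunity, and raised ANA in mice at about 300-fold the maximum clinical dose.
- That 62.5% of risk is uncounted. Only calendar time is known.
- That late events are unmonitored. They are seen, recorded and reviewed, but not counted toward stopping.

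The finding rests on the literal reading, which may not be the intended one. Minor severity; a cheap improvement.

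**What to change.** In section (6)i.m, Vaccine Toxicity, replace the scope of the count with:

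*The rule applies from the first DC vaccination through the week 17 (Arm 1) or week 25 (Arm 2) visit, or the last visit if earlier; events in Arm 2's placebo phase are not counted. After the last DC vaccination, DLTs count if at least possibly related to vaccine or to a DTH test containing vaccine components; a positive DTH reading alone is not a DLT.*

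Add that DLTs are counted when they become known and that enrolment does not wait for the window to close. Do not extend the count to week 29 or 37: only patients selected for responses or adverse events are followed that long, so the window would depend on outcome. DLT grades, the four boundaries and the Grade 3 hold stay as they are, and counting during dosing is not loosened.

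The cost is a short amendment. The visits, DTH readings and recording of Grade 2 signs and symptoms are already planned. There are three drawbacks:

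- The rule may trigger slightly more often.
- Late events may be counted after others have been dosed. At 16 patients in 12 months, 16/52 × 10 ≈ 3 more enrol during one patient's 10 post-dose weeks.
- Attribution after dosing is made by an unblinded investigator.
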